## Abstract

**Background:**

Age-related bone loss is asymptomatic, and the morbidity of osteoporosis is secondary to the fractures that occur. Common sites of fracture include the spine, hip, forearm and proximal humerus. Fractures at the hip incur the greatest morbidity and mortality and give rise to the highest direct costs for health services. Their incidence increases exponentially with age.

Independently changes in population demography, the age - and sex- specific incidence of osteoporotic fractures appears to be increasing in developing and developed countries. This could mean more than double the expected burden of osteoporotic fractures in the next 50 years.

**Methods/Design:**

To assess the predictive power of the WHO FRAX™ tool to identify the subjects with the highest absolute risk of fragility fracture at 10 years in a Spanish population, a predictive validation study of the tool will be carried out. For this purpose, the participants recruited by 1999 will be assessed. These were referred to scan-DXA Department from primary healthcare centres, non hospital and hospital consultations. Study population: Patients attended in the national health services integrated into a FRIDEX cohort with at least one Dual-energy X-ray absorptiometry (DXA) measurement and one extensive questionnaire related to fracture risk factors. Measurements: At baseline bone mineral density measurement using DXA, clinical fracture risk factors questionnaire, dietary calcium intake assessment, history of previous fractures, and related drugs. Follow up by telephone interview to know fragility fractures in the 10 years with verification in electronic medical records and also to know the number of falls in the last year. The absolute risk of fracture will be estimated using the FRAX™ tool from the official web site.

**Discussion:**

Since more than 10 years ago numerous publications have recognised the importance of other risk factors for new osteoporotic fractures in addition to low BMD. The extension of a method for calculating the risk (probability) of fractures using the FRAX™ tool is foreseeable in Spain and this would justify a study such as this to allow the necessary adjustments in calibration of the parameters included in the logarithmic formula constituted by FRAX™.

## Background

### Epidemiology of osteoporotic fractures

Osteoporosis is an asymptomatic disease until it is complicated by a bone fracture occurring without trauma or after a minimum trauma. It is the most common bone disease in humans and represents an important health care problem in developed countries. The high incidence of osteoporosis worldwide and its main complication, osteoporotic fractures, also known as fragility fractures, have been recognised for more than 20 years [1]. One of the first meta-analyses on fracture risk published in 1996 demonstrated the association between bone mineral density (BMD) and the risk for osteoporotic fracture [2].

The probability of a woman with menopause presenting an osteoporotic fracture during the remainder of her life (the most frequent are; vertebral, forearm, humerus or hip) surpasses even the risk of having breast cancer, with this probability being approximately 40% higher in developed countries and very close to the risk of coronary disease in the same countries [3].

According to the recent guidelines by the American College of Physicians for the screening of osteoporosis in males, this disease is considered to be underdiagnosed and under-treated, perhaps due to the relatively lower frequency. A 60-year-old white man has a 25% risk of having an osteoporotic fracture during his lifetime, with even more severe consequences than in women [4]. Indeed, the post-hip fracture mortality at one year in men is double that in women [4]. The influence of fragility fractures on the quality of life of both men and women has also been widely reported [5].

According to data estimated in subjects over the age of 50 years in Europe in the year 2000, 620,000 new hip fractures, 575,000 shoulder fractures, 250,000 proximal humerus fractures and 620,000 symptomatic vertebral fractures were reported, representing almost 35% of the fractures described in the world [6]. The direct costs of osteoporotic fracture in Europe are of around a total of 36 billion Euros per year [7].

The greatest clinical relevance of osteoporosis is constituted by osteoporotic fractures, and these are implicated in the increase in morbimortality and loss of quality of life attributable to this disease. Thus, attention must be focused on the identification of patients with a high risk of fragility fracture [8], than on the identification of those with osteoporosis, diagnosed exclusively by densitometry.

Although BMD (measured by densitometry) is an important component of fracture risk, several other risk factors have also been demonstrated to greatly contribute to the risk of fracture and should be taken into account when performing a global evaluation of risk [8].

### Clinical determinants of osteoporotic fracture

In the last years different studies have been carried out with the aim of identifying the clinical risk factors which may be used in the search for therapeutic strategies, with or without the use of densitometry [9].

The last version of the European guidelines for the diagnosis and treatment of osteoporosis in postmenopausal women published in 2008 [10] proposes the strategy of evaluation together the results of densitometry and clinical risk factors of fracture to decide which diagnostic and therapeutic interventions to implement.

### The FRAX ™ tool, a useful tool for clinical practice

In 2008, the WHO published a new promising tool for the evaluation of absolute risk of fragility fracture: the FRAX™ tool [11], WHO fracture risk assessment tool. This is a scale including 11 of the clinical risk factors which have demonstrated a strong association with the incidence of fracture in previous studies according to the WHO experts. Factor number 12 in this scale also includes a single value of Dual-energy X-ray absorptiometry (DXA) central bone densitometry: the T-score of the femoral neck. An introducing these data of a patient provided in the form of the FRAX™ website, an individualised calculation of the percentage of prediction of absolute risk of: (a) major osteoporotic fracture (clinical vertebral, hip, forearm or humeral fracture) and (b) hip fracture in the following 10 years may be made [11].

To develop the logarithmic formula of FRAX™, were included parameters from different European cohorts from the EVOS study focused on vertebral fractures [12]. As representatives of the Spanish population were included people from Oviedo and other three Spanish cities. However, they had very low rates of response: in some cases were less than 8%, with a total number of subjects potentially insufficient to be representative of Spanish population [13].

On the other hand, it should be pointed out that as recommended in the description of the FRAX™ tool, this scale should be developed and validated in each country. Cost-effectiveness studies are also recommended with the data from each country to obtain an approximation of the cost which each country is willing to accept as reasonable for the prevention of fragility fractures.

It is therefore reasonable for the first step before the generalised use of the FRAX™ scale in the medical offices of our country to carry out the validation of this scale in a larger cohort made up of the patients usually attended at the different health care levels in which diagnostic; treatment and follow up interventions for osteoporosis are undertaken. On the other hand, recent evidence [14-17] also recommend the evaluation of other risk factors related to low mass and risk of fragility fracture and not considered in the FRAX™ tool when assessing fracture risk such as the presence of chronic obstructive pulmonary disease (COPD), the use of some drugs such as aromatase inhibitors (increasingly more frequent in women treated for breast cancer), daily calcium intake and usual physical activity which are related to bone mass and risk of fragility fracture.

### Falls and fragility fractures

Fragility fractures are defined as those which occur after non major impact produced by a fall from a height of less than that of the patient with no added inertia to that of the displacement of its foot when walking.

Since more than 20 years ago studies have demonstrated the importance of falls on the incidence of new fractures in predisposed subjects, with a strong association between the number of falls and fracture. This association is even more important in patients over the age of 75 years than the classical association described between osteoporosis and fracture [16]. Different variables related to the greater risk of falls have also been reported such as factors of the individuals themselves (muscular strength of the lower extremities, equilibrium or postural competence, difficulties in vision, cognitive deterioration), purely environmental factors (home lighting, rugs, pets...) and iatrogenic factors (different groups of drugs, drug combinations) [18-21].

Despite these evidence on the potential influence of falls on the occurrence of fragility fractures, they have not been included as risk factors in the FRAX™ tool for the determination of absolute fracture risk at 10 years, probably due to the publication of studies with contradictory long term results which impede consistent establishment of their association.

The importance of being able to determine the association between the number of falls and the appearance of fragility fracture may be established by the possibility of their prevention, thereby reducing the risk of falling. Different studies have presented good results with different training techniques and a recent Cochrane review [22] provides measures of the potential benefit of interventions such as programmes of multidisciplinary detection and intervention (RR 0.73;CI 95%: 0.63-0.85), muscular strengthening and balance retraining (RR 0.80; CI 95%: 0.66-0.98), evaluation and modification of risks at home (RR 0.66; CI 95%; 0.54-0.81), withdrawal of psychotropic drugs (RR 0.34; CI 95%: 0.16-0.74) and a 15-week intervention of Tai Chi group exercises (RR 0.51; CI 95%: 0.36-0.73) among others.

The latest guidelines published in our country recommend intervention related to the risk of fall in subjects with osteoporosis according to a maximum grade of evidence (SEIOMM Guidelines 2008, AATRM Guidelines) [23,24].

The high incidence of falls in the elderly (30% of subjects over the age of 65 years living at home fall every year) [22], as well as the associated morbidity and the tests available demonstrate the relevance of a study such as this to establish their association and determine the need for their inclusion as important and preventable risk factors in tools such as FRAX™ to assess the absolute risk of osteoporotic fractures.

FRAX™ is a tool which is evolving and in the future may become a commonly used tool in medical centres in our country, especially in Primary Care (PC) in which the greatest number of subjects with osteoporosis is attended and where programmes of prevention of osteoporotic factors may be carried out. This is another argument reinforcing the need for urgent validation of this scale in our country, and it is the main objective of this study.

## Objectives

### Main objective

To determine the predictive validity of the WHO FRAX™ risk scale to identify subjects with the greatest absolute risk of fragility fracture in the next 10 years in a Spanish population in a clinical cohort designed to promote the study of different risk factors of presenting osteoporotic fractures.

### Secondary objective

To analyse the association between clinical and environmental risk factors (number of falls, exposure to drugs, dietary calcium intake) and the occurrence of osteoporotic fracture in a susceptible Spanish population.

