## Study population

Urban setting. Primary care (PC), extrahospitalary (E) and hospital specialties (H).

Integrants of the FRIDEX cohort. Randomised sample (simple computerised randomisation stratified by sex) of men and women from 40 to 90 years of age in the FRIDEX cohort for 10 years since the baseline DXA and QRF. At the end of 2009 this sub-cohort included 5,813 persons recruited from January 1 to December 31, 2000.

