## Overview of outcome measurements

### Data collection

The baseline variables of both BMD and QRF were collected at the time of inclusion (2000). The follow up variables (fractures and incidental falls) will be collected by telephone questionnaire (TQ) during 2010 and the beginning of 2011 to complete the 10 years of follow up. The TQ will collect data regarding the fractures occurring from the time of inclusion until the date of the TQ as well as other information on known factors of fracture risk.

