### Follow up variables

These variables include the appearance of incidental fracture in the last 10 years (dependent variable): the telephone questionnaire will be carried out with a telephone call made after 10 years of follow up. All the fractures will be confirmed through medical records and/or consultations to the health care centres after receiving authorisation from the participants. In all cases the follow up at 10 years will be completed in these subjects. In cases of death, the data related to the cause of death and the appearance of fractures will be requested from the relatives and by record checking.

The number of falls during the last year will be determined with the TQ. Review of the literature has shown different ways to analyse the falls occurring in the study subjects. The most frequently used method is considered in this study which asks about the number of falls during the year prior to the interview and whether a fracture was produced in any of the falls. Other variables to be collected during this period are: the appearance of important diseases, the taking of osteopenic drugs and the use of walking aids. Additional file 2 shows the telephone questionnaire.

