### Study limitations, potential limitations and biases

Since the FRIDEX cohort is constituted by subjects requiring a DXA scan (according to their physician), it likely that the recruited population will be at a baseline risk greater than that of the general population. Nonetheless, descriptive analysis of the population of this cohort indicates that the percentage of 32.3% of persons with densitometry osteoporosis is very similar to that reported in the literature for women of 50 years of age. Our results may therefore be extrapolated to a population in which the physician is evaluating the risk of low bone mass or fracture (case finding) which is, furthermore, the population recommended for investigation by the WHO.

The QRF used includes the variables of the FRAX™ scale and is complemented by the follow up telephone questionnaire on fractures, falls and new medications prescribed as well as diseases developed in the last 10 years.

The variable "number of falls" was not collected at the beginning of the FRIDEX cohort. Therefore, it may only be considered as an outcome variable in the subgroup of cases with incidental fractures posterior to the collection of this variable. Nonetheless, according to the opinion of the external assessor and the research team, this variable is highly related to the risk of fracture and thus, should be collected and taken into account in this study.

To minimise the effect of possible losses which may imply bias (given the morbimortality associated with fractures and the possible dropouts over 10 years), notable increases in the sample size have been considered necessary such as the cases to be localised among those with a contact telephone number. We believe that this will minimise the losses to follow up or refusal to participate for several reasons: information will be collected by telephone to avoid the difficulties of post questionnaires, which have low response rates in our setting; in addition the participants in the FRIDEX cohort had already accepted to participate in the QRF and almost all of the persons contacted in the pilot study accepted to answer follow-up survey.

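### The falls part of the secondary objective cannot be estimated as a predictor of fracture, because falls are recorded only for the final year, after most of the fractures have occurred

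*Protocol article*

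**What the plan says.** Five places in the protocol article bear on this.

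- **Secondary objective.** Number of falls is the first of three named factors in the "association between clinical and environmental risk factors (number of falls, exposure to drugs, dietary calcium intake) and the occurrence of osteoporotic fracture".
- **Background, Falls and fragility fractures.** The purpose given for studying falls is to establish the association and "determine the need for their inclusion as important and preventable risk factors in tools such as FRAX™".
- **Data collection.** "The TQ will collect data regarding the fractures occurring from the time of inclusion until the date of the TQ". The sub-cohort was "recruited from January 1 to December 31, 2000", and the interviews run through 2010 into early 2011.
- **Follow up variables.** The falls item "asks about the number of falls during the year prior to the interview and whether a fracture was produced in any of the falls".
- **Study limitations.** The falls variable "was not collected at the beginning of the FRIDEX cohort", so "it may only be considered as an outcome variable in the subgroup of cases with incidental fractures posterior to the collection of this variable". The same paragraph nevertheless concludes that it "should be collected and taken into account in this study".

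The Abstract and the Baseline variables section place dietary calcium and drug use at baseline.

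**The concern.** A factor can be assessed as a predictor only if it is measured before the outcome, or can at least be placed before it. Here the outcome window closes on the day falls are first recorded. For most participants with a fracture, the falls reported describe the period after the fracture. For those who fractured in the final year, the fall and the fracture may be one event.

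The objective and the Background section invite a reader to take any falls-fracture association as evidence for adding falls to a clinical risk tool. An association from these data could arise in several ways that say nothing about prediction:

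- a fracture leads to more falls later;
- one event is counted on both sides;
- a lasting tendency to fall was present throughout;
- people who have fractured recall falls better;
- only those alive at year 10 have a comparable last year. For deaths, the article mentions asking relatives about cause of death and fractures, but not falls.

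**Working it through.** **Plan's own figure.** None is given for the falls analysis. The sample size of 1,070 belongs to the main objective and is used here only to scale counts. With an assumed incidence of 0.5, since none is stated, 1.96² × 0.25 / 0.03² = 1,067.1, or 1,068 rounded up, which agrees closely with 1,070.

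**Step 1: order of the windows.**
- Fractures: year 0 to the interview at T, with T about 10 to 11 years (recruitment in 2000, interviews in 2010 to early 2011).
- Falls: T − 1 to T.
- Fractures after falls are collected: after T, where no outcome is described.

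With T = 10, nine of ten years of outcome time precede the falls window.

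**Step 2: share of first fractures, not of time.** Fracture incidence rises with age, so events may fall later than time alone suggests. Let R be the 10-year risk and H = −ln(1 − R). The cumulative hazard is H·t/T if the hazard is constant. If it doubles every d years, it is H·(e^(gt) − 1)/(e^(gT) − 1), with g = ln 2/d. With F(t) = 1 − exp(−cumulative hazard), the share in the last year is [F(T) − F(T − 1)]/F(T).

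Example with R = 10%, T = 10, constant hazard: H = 0.1054, F(9) = 1 − exp(−0.0948) = 0.0905, so the share is (0.1000 − 0.0905)/0.1000 = 9.5%.

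Over R from 5% to 30% and T of 10 or 11 (all assumed):

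| Hazard | Share of first fractures inside the falls year |
|---|---|
| Constant | 8–10% |
| Doubling every 10 years | 11–13% |
| Doubling every 5 years | 14–17% |

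So about 83% to 92% precede the falls window. With 1,070 people and R = 10%, about 9 to 18 of 107 first fractures fall inside it.

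**Step 3: what reverse causation alone could produce.** Suppose falls have no effect on fracture and 30% of fracture-free people fall in the year (the Background figure for people over 65 living at home). Suppose also that 90% of fractures precede the window and an earlier fracture multiplies later fall risk by m (assumed). Fall prevalence among cases is 0.9 × 0.30m + 0.1 × 0.30, and the odds ratio compares this with 0.30.

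- m = 1.00: 0.300, odds ratio 1.00
- m = 1.25: 0.3675, odds ratio 1.36
- m = 1.50: 0.435, odds ratio 1.80
- m = 2.00: 0.570, odds ratio 3.09

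**Step 4: what event overlap alone could produce.** Set m = 1 and let every last-year fracture bring its own counted fall. With share s in the window, prevalence among cases is 0.30(1 − s) + s.

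- s = 8%: 0.356, odds ratio 1.29
- s = 10%: 0.370, odds ratio 1.37
- s = 17%: 0.419, odds ratio 1.68

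This is an upper bound for overlap. The Background defines fragility fracture through a fall, but it also describes fractures without trauma.

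**The case against.** The strongest reply is that the authors saw the problem. The limitations section states that falls were not recorded at baseline and restricts their use, and part of the remedy below follows that restriction. The Analysis plan never names falls as a covariate in the Poisson model, so no faulty model is actually specified. The item on whether a fall caused a fracture would help separate overlapping events. The passage on FRAX is background motivation rather than a decision rule.

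Much of this is fair, but it does not remove the point. The restriction allows falls only for fractures after their collection, and the described follow-up contains none. Falls are a risk factor in the objective and an outcome variable in the limitations. A later analysis plan can choose the model, but it cannot supply earlier falls that were never recorded.

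Three stronger readings are tempting and are not supported.

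- **That the whole secondary objective fails.** It does not: calcium and drugs are recorded at baseline and keep the right time order. Some drug use is also asked about at year 10, but nothing says those reports will serve as exposures.
- **That the result would be reverse causation.** It could be. Step 3 gives an odds ratio of 1.00 if fracture does not raise later falls, and the documents fix neither the direction nor the size of the bias.
- **That later fractures can never be obtained.** The Ethics section seeks consent for further calls, although no later fracture outcome or analysis is described.

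**Conclusion.** The concern holds for the falls component only. As designed, number of falls cannot be estimated as a predictor of fracture, and an association with last-year falls would not support a decision on adding falls to FRAX. The time order follows from the article alone. The 83% to 92% rests on the assumed hazards and risks in step 2, and large majority is the safe wording. The odds ratios in steps 3 and 4 illustrate what non-predictive mechanisms could produce and are not estimates of bias in this cohort. Disclosure in the limitations section does not settle the matter while the objective and the Background aim still say otherwise. The main objective, the validation of FRAX, is untouched.

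**What to change.** 1. **Secondary objective:** remove number of falls from the list of risk factors, and keep drug exposure and dietary calcium.
2. **Analysis plan:** report last-year falls descriptively, or as an outcome compared between people with and without an earlier fracture. Exclude falls that caused the counted fracture, using the questionnaire item that already asks about this.
3. **Background aim:** make any statement about adding falls to FRAX conditional on fractures occurring after the interview, if the further calls foreseen under Ethics are used to collect them.
4. **Limitations:** reconcile the paragraph with the revised objective, and say that the permitted subgroup is empty unless follow-up continues.

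The cost is wording. No change to the sample or the questionnaire is needed, and one secondary conclusion that the data cannot support is given up. Any later collection of fractures would be additional work and is optional.
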